## Abstract

**Introduction:**

This paper presents the protocol for the effectiveness-implementation trial: Systems Thinking with Active Implementation Research (STAIR) for childhood obesity prevention. STAIR’s objective is to protect primary school children in Victoria, Australia from unhealthy weight and test implementation strategies for sustaining healthy school environments. STAIR is a 3-year cluster-randomised controlled trial with repeat-cross-sectional child-level data collection utilising an effectiveness-implementation type-1 hybrid design. Schools will be recruited from non-metropolitan government primary schools in Southwest Victoria, Australia, with consenting schools (target = 28) randomly assigned (1:1) to intervention or control, and students in grades 1–6 (n = 3000–6000) recruited using an opt-out approach.

**Intervention:**

The intervention, co-designed by each school community, will involve multi-step group model building and action formulation process using community-based systems dynamics and baseline data (i.e., child weight status, HRQoL, health behaviours, and school environment characteristics). Implementation strategies will be guided by an active implementation framework, and coordinated by a leadership team of school representatives, community partners, and researchers.

**Primary and secondary outcome measures:**

Primary outcomes are to measure (1) change in standardised body mass index (z-BMI) between intervention and control groups after three year and (2) change in acceptance and adoption of STAIR interventions and support. Secondary outcomes include differences in obesity prevalence, health behaviour measures and HRQoL, between intervention and control groups after three years. Implementation outcomes will focus on strategy effectiveness, acceptability, and utilisation. Secondary data will be collected from schools and partner organisations. An economic evaluation will assess the cost-effectiveness of intervention and implementation support.

**Conclusion:**

STAIR aims to create lasting changes in schools to prevent childhood obesity by supporting healthy environments and providing insights into interventions’ cost-effectiveness and feasibility. The findings will guide policymakers and educational institutions in adopting sustainable health promotion strategies.

**Trial registration:**

ANZCTR-ACTRN12624000461594p

## Introduction

The case for action to prevent childhood obesity is compelling [1]. One in 4 children in Australia experience overweight or obesity. Prevalence has steadily increased from the 1980s to the 2000s and is unequally distributed socio-economically and geographically [2]. Children with obesity are stigmatised because of their weight, have a lower quality of life [1,3], have lower mastery of movement skills, and have more physical and psychosocial disability than their healthy-weight peers [4–6]. Unhealthy diets and insufficient physical activity are risk factors for child obesity, and obesity itself, endures into adulthood, putting children with obesity at risk of chronic diseases, such as type 2 diabetes, later in life [7,8]. Furthermore, adults living with obesity experience higher medical expenses, discrimination, and worse jobs [9]. Living with obesity is the leading contributor to the burden of disease in Australia, and the total cost was estimated at $1280 (US$940) per capita in 2019 [10]. Reviews of strategies for managing and treating obesity in childhood indicate they have limited effectiveness and can be costly and invasive [11–13].

The UN Convention on the Rights of the Child indicates that ‘children have the right to the best health care possible, clean water to drink, healthy food and a clean and safe environment to live in’ [14]. Interventions have been implemented in different settings including schools to create a healthy and safe environment. The most recent Cochrane review on childhood obesity prevention found changing diet and activity levels, particularly in school settings, can be effective in reducing standardised BMI scores in children aged 6–12 years [15]. The review acknowledged that the complex and dynamic determinants of childhood obesity require a systems approach involving interventions targeted at different parts of the system, leading to coordinated policy initiatives across various government departments [16].

In Australia, the national obesity prevention strategy has adopted such an approach [17], and our group has contributed to evidence of effectiveness. The research team’s latest trials (WHO STOPS, 2015–2019) [18] and (RESPOND 2019–2024) [19], drew on community-based systems dynamics to co-develop intervention actions, in line with recommendations from the Lancet Commission on the Global Syndemic of Obesity, Undernutrition, and Climate Change [20]. Community-based systems dynamics offers significant advantages over earlier approaches to intervention design by providing a communal and visualised understanding of local causes of childhood obesity and the complex interactions between them, and by achieving community proprietorship of and engagement in, prevention strategies [21]. It enhances rather than replaces existing activities and communities can identify and intervene in elements of the system where they can have the most impact. The WHO STOPS study achieved a 4% reduction in overweight and obesity prevalence and improved health-related quality of life (HRQoL) in intervention communities compared to no change in controls in the first two years of the trial [22]. However, while HRQoL and dietary changes were sustained after 4-years, weight status changes, which were similar in magnitude to other studies [15] were not. Other community-based interventions have also seen intervention effects on weight dissipate over time [23], and we think the reason is waning implementation support.

A recent systematic review identified ten characteristics for sustained implementation of community-based interventions, including leadership, workforce development, community engagement, partnerships, communication, policy, adaption, evaluation, resourcing, and governance. In WHO STOPS, the two-year time point coincided with a reduction in support from the research team (removal of trained staff available to support implementation) [18]. We hypothesised that this reduction in implementation support was the primary reason the intervention effect was not sustained as community capacity was low (e.g., too few staff, competing priorities). An unpublished audit conducted by the research team among rural-based communities, including WHO STOPS [24] and RESPOND [25] communities, revealed that rural prevention services were understaffed in Victoria, with only 1.4 full-time equivalents for every 10,000 people. For comparison, Australia has 37 doctors for every 10,000 people. Further, support available to schools in Victoria is largely online. Wolfenden *et al* identified that the complexity of the environment the community-based health service partners operate in is not well understood (size and diversity of the workforce, types and levels of training; mix of public and private organisations involved; mix of local, state and federal governance and funding structures) [26]. These implementation factors are also poorly measured, in part because researchers haven’t known what to measure. Collectively these observations reveal a tension between the expectations of researchers and policymakers on communities and their capacity to implement interventions, coupled with a scarcity of data on implementation [27].

In the face of low implementation capacity and competing priorities (such as responding to COVID-19) and increasingly obesogenic environments (such as advertising of unhealthy food) [28,29] we contend that communities, and particularly schools, need implementation support to sustain healthy environments. Working with school communities rather than whole communities may help focus implementation support and minimise competing priorities. Also, the Lancet Commission encourages greater application of expert-facilitated (not owned) implementation [20]. Our research has demonstrated it is possible to create environments that protect children from obesity and others have shown that healthy weight can persist after children have participated in school-based interventions [30,31]. However, there is a paucity of research exploring whether system-wide changes to school environments can be sustained so that successive cohorts of children are protected from unhealthy weight gain.

The primary objective of this study is to protect primary school children in rural Victoria, Australia, from unhealthy weight and test implementation strategies for sustaining school environments that promote health and wellbeing. The research questions being addressed in this study are: (1) can Victorian school communities be supported to prevent unhealthy weight gain for 3 years and; (2) what are the optimal implementation strategies to support delivery and maintenance of the intervention in schools? It is hypothesised: (1) a reduction of 0.13 units in z-BMI will be achieved in intervention schools relative to controls after 3 years of intervention and; (2) that implementation strategies will be cost-effective, acceptable, utilised, appropriate, feasible, delivered as intended and maintained in intervention schools.

## Methods and analysis

### Conceptual framework

Obesity prevention research is at the point where substantial knowledge about how to prevent childhood obesity is available but where that knowledge is not applied in practice [32]. The Interactive Systems Framework (ISF) was designed to facilitate the dissemination and implementation of such prevention knowledge. Given the gaps identified in implementation support for previous interventions, we used ISF to conceptualise a prevention support system (Fig 1). Obesity prevention will be the innovation we intend to disseminate and implement, school communities will be the prevention delivery system, and the research team will be the prevention synthesis and translation system (Fig 1). Trial partners, named below, are key stakeholders in this system. STAIR intends to strengthen prevention support and delivery systems (capacity in schools and among partners). Researchers in the field of applied implementation science have recognised the need to help communities translate prevention into practice and have developed frameworks and strategies to support this [33,34]. STAIR will use the Active Implementation Framework developed by Fixsen [35] to support schools so intended prevention outcomes (healthy weight, HRQoL) will be achieved and sustained. This framework was chosen as it emphasises system-wide change, active problem-solving, and on-going learning. It defines for the trial an executive and sponsorship function, a cross-system leadership team to coordinate and build overweight/obesity prevention capacity and quality, and outcome monitoring functions to ensure delivery of intended outcomes [36]. To complete the conceptual framework, we will place group model building (GMB), the co-design process from community-based systems dynamics [37], at the centre. Students, staff, and partners, will map the causes of childhood overweight/obesity and identify solutions and implementation strategies using GMB.

**Fig 1 pone.0325853.g001:**
[figure not shown]
Conceptual framework.

### Ethics and dissemination

Approval has been obtained from the Deakin University Human Research Ethics Committee (ID: 2024_051) and the Victorian Government Department of Education and Training (ID: 24-02-254). We had intended to recruit from Government and Catholic schools, but the Diocese of Ballarat Catholic Education Office did not approve the project, citing that the project did not align with the Diocese’s priorities, so we are continuing this study using Government schools.

### Trial design and status

The STAIR project, conducted over five years with three intervention years, will comprise a cluster randomised controlled trial with repeat-cross sectional data collection, utilising an effectiveness-implementation type-1 hybrid design. Fig 2 shows the Standard Protocol Items: Recommendations for Intervention Trial (SPIRIT) schedule of enrolment, interventions, and assessments along with timelines (S1 Fig).

**Fig 2 pone.0325853.g002:**
[figure not shown]
SPIRIT Schedule and timelines.

Participant recruitment and data collection have not begun. School recruitment for this study is planned to commence on 28/04/2025.

### Setting and recruitment

All government primary schools in southwest education region of Victoria excluding schools in the Brimbank, Melton and Western Melbourne education areas, schools participating in other overweight/obesity prevention interventions (as advised by Victorian Government Department of Education and Training), schools with fewer than 120 children and schools exclusively educating children with special needs will be eligible to participate in the trial. A randomly sorted list of all eligible Government schools (n = 97) will be generated using a random selection without replacement. Starting at the top of the list, school principals will be contacted by the research team, provided with information about the study and invited to provide written informed consent. Up to three follow-up phone calls and/or in-person visits will made to gain consent before moving on to the next school on the list. Recruitment will continue until 28 schools have consented (assuming a 33% recruitment rate). Previous studies in the region suggest school participation rates of 70% and student participation >80% [18].

### Randomisation and blinding procedure

After the full sample of schools is recruited schools will be randomly allocated (1:1), to intervention or control groups within strata defined by size (student enrolment ≥120). The study statistician will produce the random sequences and allocation will occur simultaneously for all schools. Given the nature of the intervention, it will be impossible to conceal the allocation from the school communities. However, data analysts will be blind to intervention allocation by removing school identification data.

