### Sample size calculations

Victorian Government Department of Education summary statistics compiled in 2023 indicate that, in the 21 regional and remote LGAs of the Southwestern Department of Education region (excluding schools on the geographical fringe of Melbourne in Brimbank, Melton, and Western Melbourne education areas), there were 57,828 children in primary schools. A total of 47,087 (81.4%) children attended the 147 eligible schools with an average of 320 students per school. By recruiting 28 schools and accounting for a 20% school dropout rate, it is anticipated that data will be collected across all time points (baseline, year 1, year 2 and year 3) in 22 schools. A sample of 22 schools, with approximately 200 participating students per school, will provide 83% power to detect a difference of 0.13 units in the primary outcome (z-BMI) between study groups; assuming z-BMI standard deviation 1.1 and intra-cluster correlation coefficient 0.02, as found in the WHO STOPS trial in a comparable population [22,70]. An effect size of 0.13 units in z-BMI it was shown to be achievable, using similar intervention methods, after 2 years in the WHO STOPS trial. Power was estimated using Shiny CRT calculator based on a cluster randomised parallel design with baseline measure, cross-sectional samples, and exchangeable correlation structure (α = 0.05) [71].

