### Statistical analysis

Students will be the unit of observation for effectiveness analyses and analyses will be conducted under the intention-to-treat principle. The effect of the STAIR intervention on the z-BMI will be assessed using a linear mixed model with study group, time (baseline, year 1, year 2, year 3), and the interaction group × time as fixed effects. School and student will be included as random effects to account for clustering of students within schools and repeated measures in students measured more than once). Secondary outcomes will be analysed by fitting a generalised linear mixed model with link and distribution selected according to the outcome distribution. Whether age modifies the intervention effect will be explored using the same modelling approach including additional interaction terms. The environmental audit, and implementation outcomes will be analysed at the school level using descriptive statistics and thematic analyses.

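### The only size stratum for randomisation (enrolment ≥120) repeats the eligibility threshold, so all 28 schools share one stratum and the allocation as written is unstratified

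*Protocol article*

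**What the plan says.** Setting and recruitment lists, among the schools that cannot take part, "schools with fewer than 120 children and schools exclusively educating children with special needs". Every eligible school therefore has at least 120 children. The same section says "Recruitment will continue until 28 schools have consented".

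Randomisation and blinding procedure states: "After the full sample of schools is recruited schools will be randomly allocated (1:1), to intervention or control groups", and adds that this is done "within strata defined by size (student enrolment ≥120"). All schools are allocated at the same moment. No second size category, other cut-point or other stratification factor appears anywhere in the article.

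Sample size calculations says that "children attended the 147 eligible schools with an average of 320 students per school". Sizes must therefore vary well above the floor of 120. Statistical analysis describes the z-BMI model as a "linear mixed model with study group, time (baseline, year 1, year 2, year 3), and the interaction group × time as fixed effects", with school and student as random effects.

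**The concern.** A stratification factor must divide the units being randomised. Here the stratum rule and the eligibility rule use the same measure and the same threshold, so the rule cannot divide them. The plural used for the strata shows that at least two size groups were meant. Either the intended cut-point is not the one printed, or 120 remains from a design that admitted smaller schools. The article does not settle which.

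Two things are at stake. First, with only 28 clusters, chance can put most of the larger schools in one arm, and size is the one feature the sponsor chose to guard against this. Second, the trial report would describe a stratified allocation that did not take place. Allocation happens once, so neither can be repaired afterwards.

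**Working it through.** **1. Stratum membership.** Eligible means enrolment of at least 120. The stated stratum is enrolment of at least 120. So 28 of 28 schools are in it and 0 of 28 are below it. Allocation 1:1 within a single stratum of 28 is unstratified 14:14.

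**2. Does the stated power depend on stratification?** Inputs from Sample size calculations: 22 schools (k = 11 per arm), m = 200 students per school, SD 1.1, ICC 0.02, difference 0.13, α = 0.05 (taken as two-sided), and a parallel cluster design with a baseline cross-section and exchangeable correlation.

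- Design effect: 1 + (m − 1) × ICC = 1 + 199 × 0.02 = 4.98
- Correlation of a school's baseline and follow-up means: r = m × ICC / 4.98 = 4 / 4.98 = 0.803
- Variance: 2 × 1.1² / (11 × 200) × 4.98 × (1 − 0.803²) = 0.0011 × 4.98 × 0.355 = 0.00194, so SE = 0.0441
- Power: Φ(0.13 / 0.0441 − 1.96) = Φ(0.99) = 83.9%

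A t reference with 42 degrees of freedom gives 82.1%. The stated 83% lies between the two, so it is reproduced. No stratification term enters the formula, so the figure does not change.

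**3. Balance of larger and smaller schools.** Suppose 14 of the 28 schools are larger and 14 smaller. This split is an illustration and is not in the documents. Under unstratified 14:14 allocation, the number X of larger schools in one arm is hypergeometric: P(X = x) = C(14, x)² / C(28, 14), with C(28, 14) = 40,116,600.

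- 7:7 split: 3,432² / 40,116,600 = 29.4%
- 8:6 in either direction: 2 × 3,003² / 40,116,600 = 45.0%
- 9:5 or worse: 100% less these two, before rounding = 25.7%
- 9:5 exactly, in either direction: 2 × 2,002² / 40,116,600 = 20.0%, which leaves 5.7% for 10:4 or worse

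A stratum that separates the two groups fixes the split at 7:7.

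**4. Balance of total enrolment.** The article gives a mean of 320 but no spread. Assumption: enrolment = 120 + a gamma variable, overall mean 320, coefficient of variation (CV) 0.4, 0.5 or 0.6. There were 20,000 simulated allocations per setting. The event is a larger arm total more than 1.2 times the smaller.

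| Assumed CV | As written (unstratified) | Median-split strata (7:7 in each) |
|---|---|---|
| 0.4 | 23% | 7% |
| 0.5 | 33% | 15% |
| 0.6 | 42% | 26% |

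A shorter run of 5,000 gave 22%, 34% and 43% as written, and 7%, 15% and 25% with the median split. The difference is simulation error.

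**5. Effect on precision.** In the same simulated schools, take participants as enrolment × 200/320 and weight each school by its information from the variance formula in step 2. Relative to the median split, unstratified allocation raises the mean variance of the effect by 0.3%, 0.4% and 0.5% for the three CVs. The 95th percentile of the variance ratio is 1.02, 1.02 and 1.04.

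**The case against.** The strongest reply is that the slip does little statistical harm, and much of it stands. Unstratified 1:1 allocation made simultaneously after full recruitment is a valid randomisation. It does not bias the comparison, and it still gives 14 schools per arm. The power figure never relied on stratification, and step 5 shows that precision hardly moves. A total more than 20% larger sounds serious, but a ratio of 1.2 is only a 54.5:45.5 division of children. The documents do not show that school size predicts change in z-BMI, and the primary contrast is a difference in change from baseline, so size-related differences in level do not pass straight into the estimate.

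A reader might go further than the documents allow in two ways.

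- **That a material size imbalance is likely.** The simulated rates are all below one half. They rest on an assumed distribution, and the mean of 320 belongs to 147 schools, whereas Setting and recruitment gives 97 eligible schools.
- **That the absence of a stratum term in the z-BMI model is a second error.** With one stratum there is no term to fit, so the model is consistent with the allocation as written. A stratum term is needed only once real strata exist.

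None of this removes the contradiction. The article does not leave the stratum definition to another document. It states one, and that definition cannot work with its own eligibility rule.

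**Conclusion.** The point holds as an internal contradiction between Setting and recruitment and Randomisation and blinding procedure. It follows from the two rules alone and needs no assumption. As written, the allocation is unstratified and does not control school size.

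The cost is limited to chance balance on the chosen factor and a truthful account of the design. The 25.7% figure depends on the illustrative 14/14 division. The 22 to 43% range, against 7 to 26%, depends on the assumed CV and gamma shape. Validity and the 83% power are not in question. This should be fixed before allocation, but it is not a threat to the trial's primary conclusion.

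**What to change.** Before allocation, reconcile the two sections. Replace the ≥120 stratum with a size cut-point that divides the eligible schools. One option is the median enrolment of the 28 consented schools, computed and fixed before the sequence is generated, with a rule for ties. Randomise 1:1 within the resulting strata, and include the stratum as a fixed effect in the z-BMI model and the secondary-outcome models. If no such cut-point is intended, delete the reference to strata and state that allocation is unstratified 1:1, which is also valid.

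The cost is one line in the protocol, a matching line in the randomisation program and, if strata are kept, one model term. No extra schools or data are needed. The article says school recruitment has not begun, so the change can still be made in time.
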